### Blinding

In accordance to the mode of the interventions the residents and field researchers are not blinded to group allocation. A blinded statistician not involved in the trial process will be responsible for final analysis.

### Drop-outs

Drop-outs will be documented thoroughly and included in the data analysis until the point of drop-out. Reasons for loss to follow-up and protocol deviation will be reported and analyzed both at the level of the cluster (cluster withdrawal or loss to follow-up) and the individual (resident withdrawal or loss to follow-up) [12].

### Data analysis

All analyses are based on the intention-to-treat principle, which means that each cluster and the individuals (residents) are evaluated according to their randomly assigned intervention.

Metric variables will be reported using means and standard error of measurement. For nominal or ordinal variables this will be done by reporting rates with declaration of the 95% confidence interval. The changes of the primary outcome apathy score *AES *over time and additional data taken at the other measurement points are compared between the intervention and the control group and are treated as changes in proportions or means and their standard errors, according to the nature of the variables. Hypotheses tests concerning time effects, intervention effects, and an interaction time × intervention effect are carried out.

Correlated data which occurs if the residents are nested in the same cluster can be taken into account by applying fixed and random effects models (mixed models).

All results concerning the effects of intervention are primarily evaluated on individual level.

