## Methods

### Study design

A cluster randomized controlled trial with nursing homes as clusters is designed to verify the effects of 3 individual interventions: structured reminiscence therapy, 10-minutes activation and snoezelen. In order to preclude that the effects arise only due to the intensified social contacts, analogous individual contacts are implemented in the control group via unstructured verbal communication.

It is hypothesized that the interventions will have a positive impact on apathy in long term care residents with dementia in comparison to the control group. The primary outcome measures apathy after 12 months.

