**Figure 2 F2:**
[figure not shown]
**Points of measurement and outcome measures**.

The primary outcome measure is apathy after 12 months using the German version of the *Apathy Evaluation Scale - AES *[16,17]. Data collection will be done by interviews of the nursing staff.

Secondary outcome measures on the resident level are behavioral disturbances, isolated aggressive events and well-being.

Behavioral disturbances will be measured using the *Neuropsychiatric Inventory (Nursing Home) - NPI-NH *[18]. The instrument is a caregiver-based rating scale to evaluate 12 neuropsychiatric symptoms in patients with dementia: delusions, hallucinations, agitation, depression, anxiety, apathy, irritability, euphoria, disinhibition, aberrant motor behavior, night-time behavior disturbances, and appetite and eating abnormalities. Isolated aggressive events will be continuously documented by the staff members using the *Staff Observation Aggression Scale-Revised - SOAS-R *[19]. This instrument is to monitor the frequency, nature, and severity of aggressive incidents. Well-being will be measured using a Likert-type *Smiley Face Rating Scale *- *SRS *range from 1 to 4 marks by the residents.

Socio-demographic data like age, gender, and treatment data will be assessed and documented thoroughly in a Case Report Form, including the German versions of the *Clinical Dementia Rating *- *CDR *[20,21] and the *Care Dependency Scale: Pflegeabhängigkeitsskala *- *PAS *[22,23]. As a progressive course of disease can be assumed, a final assessment to the most important treatment data (i.e., MMSE, CDR, PAS) will be done for a better interpretation of results.

As further secondary outcome measures on staff level the health-related quality of life using the *Nottingham Health Profile *- *NHP *[24,25] as well as the evaluation of the subjective work pressure with subscales of the *Potentialanalyse stationärer Altenpflege - PASTA *[26] will be measured on the basis of a self-evaluation. It can be assumed that due to the increase of successful communication and the reduction of challenging behavior in residents with dementia, physical and mental strains of caregivers will be reduced and their health-related quality of life will increase or the strain caused by their job's tasks will be reduced.

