### Sample size calculation

It is assumed that people with mild to moderate dementia have a mean apathy score *AES *of 45 [16]. To detect a mean reduction of the apathy score from 45 to 35 points (23%) with standard deviation (SD) 12 points between one intervention and one control group we need 13 residents in 10 nursing homes. The power of 80% for a cluster randomized t-test with a significance level alpha = 0.016 (0.05/3) is obtained with assumed intra-cluster correlation coefficient of ICCC = 0.05. The number of nursing homes increases to 20 (4 groups consisting of 5 nursing homes each) as there are three intervention groups and one control group and all intervention groups are tested against the same control group. Considering a mortality rate of 40%, the number of required study participants in each nursing home increases to 18 residents with dementia and thus to a total sample size of N = 360 residents (20 nursing homes * 18 residents).

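### The stated analysis compares changes in AES; a 12-month AES comparison adjusted for baseline is more precise, costs nothing, and fits the defined primary outcome

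*Protocol article*

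**What the plan says.** The protocol article defines the primary outcome twice as the level of apathy at 12 months. Study design: "The primary outcome measures apathy after 12 months". Measures: "The primary outcome measure is apathy after 12 months", using the AES.

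The Data analysis section instead takes changes in the AES over time as the quantity of interest. These "are compared between the intervention and the control group and are treated as changes in proportions or means and their standard errors". It adds: "Hypotheses tests concerning time effects, intervention effects, and an interaction time × intervention effect are carried out". Clustering within homes "can be taken into account by applying fixed and random effects models (mixed models"). Baseline AES is not named as a covariate.

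The Sample size calculation is based on a reduction "from 45 to 35 points (23%) with standard deviation (SD) 12 points between one intervention and one control group", with "significance level alpha = 0.016 (0.05/3"), 80% power, a cluster randomised t-test and an ICC of 0.05. It does not say whether 12 is the SD of a single score or of a change.

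Under Cluster randomization, the allocation list is generated only after all baseline measurements, so baseline AES is a true pre-randomisation covariate.

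**The concern.** A change score subtracts the whole baseline value, whatever its correlation with the 12-month value. Covariate adjustment removes only the part of the 12-month value that baseline predicts. Both estimate the same treatment effect in a randomised trial, but adjustment has the smaller variance whenever the correlation is below 1.

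This matters more here than in a large trial. Each comparison rests on five homes per arm, alpha is split over three comparisons, and 40% mortality is expected. Chance differences in baseline AES between arms are likely with so few homes, and a change score over-corrects for the difference actually observed. That is a loss of efficiency given the observed imbalance; it does not bias the estimate over repeated randomisation.

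The stated comparison also does not line up with the outcome definition: one is a level at 12 months, the other a change over time.

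**Working it through.** **1. Reproducing the planned 13 residents per home.**
Inputs from the Sample size calculation: difference 45 − 35 = 10, SD 12, alpha 0.016 (two-sided assumed; sidedness is not stated), power 80%, ICC 0.05, 5 homes per arm.
- A t-test without clustering needs n = 32 per arm.
- With design effect 1 + (m − 1) × 0.05, and one of the five homes per arm set aside as a small-cluster correction, m = 0.95n / (4 − 0.05n) = 30.4 / 2.4 = 12.67, rounded up to 13.

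So 13 reproduces with an SD of 12 and no baseline adjustment. Other conventions do not give it: without the correction m = 9, and a two-sided noncentral t with 8 df gives m = 17.

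**2. Relative precision.** This step does not depend on what the SD of 12 means.
Let σ be the SD of a single AES score, equal at both times, and ρ the baseline to 12-month correlation.
- Variance of change: 2σ²(1 − ρ).
- Residual variance after adjustment: σ²(1 − ρ²).
- Ratio, adjusted to change: (1 − ρ²) / [2(1 − ρ)] = (1 + ρ)/2.

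The ratio is 0.65 at ρ = 0.3, 0.75 at 0.5 and 0.85 at 0.7. It is below 1 for every ρ < 1, and the gain shrinks as ρ rises.

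**3. Power, if 12 is the SD of a single score.**
- Evaluable residents per home: 18 × (1 − 0.40) = 10.8.
- Design effect: 1 + 9.8 × 0.05 = 1.49.
- SE for the unadjusted 12-month comparison: 12 × √(2 × 1.49 / (5 × 10.8)) = 2.82.
- Test: noncentral t, two-sided alpha 0.05/3 = 0.0167, 16 df (20 homes less 4 arms).
- The SE is scaled by SD/12 for each analysis.

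| ρ (assumed) | SD of change | Adjusted SD | Power, change | Power, adjusted |
|---|---|---|---|---|
| 0.3 | 14.20 | 11.45 | 63% | 84% |
| 0.4 | 13.15 | 11.00 | 71% | 87% |
| 0.5 | 12.00 | 10.39 | 80% | 91% |
| 0.6 | 10.73 | 9.60 | 89% | 95% |
| 0.7 | 9.30 | 8.57 | 96% | 98% |

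The unadjusted 12-month comparison has 80%, the same as change at ρ = 0.5, where the SD of change equals 12. Change does worse than the unadjusted comparison only when ρ < 0.5, and better above that.

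**4. Sensitivity.**
- With 8 df (one pairwise comparison), change against adjusted is 53% against 74% at ρ = 0.3, and 69% against 83% at ρ = 0.5.
- With the intended 13 per home and the method of step 1 (normal approximation), it is 67% against 87% at ρ = 0.3, 83% against 93% at 0.5, and 97% against 99% at 0.7.

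Adjustment comes out ahead in each variant.

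**Assumptions throughout:** ρ is not in the article; it is taken to act equally at home and resident level, and the ICC is held at 0.05 on every scale.

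**The case against.** The strongest reply is that the article does not commit to a simple change-score test. The quoted sentence is generic and covers all variables. The section also plans tests of intervention and of time × intervention, and allows mixed models. A mixed model that treats baseline as a response and constrains baseline means to be equal across arms comes close to covariate adjustment in efficiency, and nothing excludes it. A full analysis plan, not shown, may name baseline AES as a covariate.

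Much of this stands: the wording does not rule out baseline adjustment. But the comparison actually described is one of changes. If baseline is one of the time points and its means are left free, the time × intervention contrast at 12 months is, for complete data, the difference in change. The intervention main effect then averages in the pre-treatment baseline. The point is therefore about a stated method that can be bettered, not about missing detail.

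A reader might also infer that the analysis contradicts the sample size calculation because a score SD of 12 was used to plan a change analysis. The article does not support this. The SD is unlabelled, and describing the effect as a mean reduction allows either reading. If 12 is already the SD of a change, there is no mismatch. If it is a score SD, change falls behind an unadjusted 12-month comparison only for ρ < 0.5, and no value of ρ is given.

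Finally, the power figures at 10.8 per home partly reflect the separate step from 13 to 18 residents for mortality. By the same 16-df method, 13 per home gives 69% for change at ρ = 0.3, against 63% at 10.8. The gap between the two analyses remains.

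**Conclusion.** The point holds as an efficiency improvement. The stated comparison of changes is valid under randomisation but less precise than a baseline-adjusted comparison of 12-month AES, and the latter matches the primary outcome as defined. Given equal variances at the two times, the variance saving is 35%, 25% and 15% at ρ = 0.3, 0.5 and 0.7. The power gain depends further on reading 12 as a score SD and on ρ: about 21 percentage points at ρ = 0.3, 11 at 0.5 and 2 at 0.7. If ρ is high, little is lost by analysing change. Neither bias nor a proven conflict with the planning SD follows from the text.

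**What to change.** In Data analysis, state that the primary analysis compares 12-month AES, each intervention against control, in a mixed model with baseline AES as covariate and a random home effect. Report change from baseline descriptively. In the Sample size calculation, say whether the SD of 12 refers to a single score or to a change.

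This costs two sentences. Baseline AES is already collected before randomisation, so no new data, visits or participants are needed.

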### Protection of data privacy

We will create a pseudonym for all participating nursing homes and residents to collect and analyze the trial data. Key lists will be stored separately from the trial data and erased after final data analysis. Data will be analyzed in a way that no conclusions can be drawn to individual participants or nursing homes. Trial data is stored in lockable cabinets in lockable rooms.

### Quality assessment

An accompanying monitoring by the investigators will assure the quality of the realized interventions and the collected data.

The trial is part of the Nursing Research Network "Mitte-Süd". A report system is established within the network. Annual quality reports have to be prepared for the German Federal Ministry of Education and Research as the funding organization.

### Publication policy

We plan to publish the trial results in a peer-reviewed, international, Medline-listed journal, independent of study results. All results will be reported within context to this study protocol and to the CONSORT statement extended to cluster randomized trials [27].

### Ethical considerations

The study protocol is approved by the ethics committee of the Medical Faculty, Martin-Luther-University Halle-Wittenberg, Germany.

Direct and indirect questioning of residents with dementia requires a particularly careful approach. Participation in the trial is voluntary and requires the consent of the residents and/or their legal guardians. Trial participants and/or their guardians will be receiving detailed information about the aims and the contents of the trial and will be referred to the application of the Federal Data Protection Act. The study will be carried out in compliance with the Helsinki Declaration.

## Discussion

Different nursing methods in the area of dementia are partly adopted in the practice with great euphoria but often without scientific evidence. Experiences show that there is therefore considerable need to identify adequate nursing methods in caring for people with dementia that are evidence-based and effective.

This trial will particularly contribute to the evidence on efficacy of non-pharmacological interventions in dementia care.
